### Data collection procedures

There will be three visits with each baby included in the study in both, control and intervention group: a visit at the start of the study (recruitment) and two follow-up visits, at three and six months after the recruitment visit (Figure 1).

The father and/or mother will be asked to provide, using an electronic data collection system created for the study, data regarding the following:

1-The baby: age, sex, breastfed/artificial milk, living nucleus, medical history and clinical data for follow-up,

2- The parents: age, sex, socio-demographic data, smoking status (yes or no). In smokers, data on the smoking habit, smoking behavior during pregnancy and whether or not the baby was breastfed, behavior during breastfeeding. Finally, smoking behavior changes during the study.

3-The degree of exposure of the baby to ETS, within and outside of the home, will be based on the questions proposed by clinical practice guidelines [13,14,35,36].

In order to measure the levels of biological nicotine in hair, a sample of the baby's hair will be taken at the first (recruitment) visit and at the last (six-month) visit. A lock of hair will be cut from the root and once collected, will be placed on a card and put into an envelope, which will be provided with the study materials (Additional files 1 and 2).

For the secondary objective, change in smoking habit in the father and/or mother, expired carbon monoxide will be measured in those that declare smoking abstinence during the study period. Cut off point: 10 ppm.

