### Study period

The preparation and pilot test period: during 2008

Data collection period: March-December 2009. The period is not coincidental; the first recruitment visit is in spring and the six-month control visit in the fall, in order to compare the degree of exposure in a similar climate period.

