### Description of laboratory analysis technique

Measuring nicotine in hair provides better information about average or long-term exposure to ETS as compared to other biological markers such as cotinine in the urine, saliva or blood, which have a shorter retrospectivity [28-32,37]. As hair grows in average at a rate of one centimetre per month, nicotine concentrations found in a segment of hair are related to the exposure during a period of time depending on the distance from the root. It is a specific biological indicator, sensitive, stable over time and temperature, not influenced by specific exposures prior to the analysis and easy to obtain [38,39]. The same IMIM team, with broad experience with the technique, analyzed all the samples. The analytical procedure of nicotine in hair utilizes ultra performance liquid chromatography (UPLC) coupled to tandem mass spectrometry (MS/MS) using a triple quadrupole instrument. The hair samples (several milligrams) are extensively washed with dichloromethane to eliminate any superficial contamination. Then hair samples are dissolved in an alkaline (1 M potassium hydroxide) solution. The nicotine released from the matrix of hair is extracted using dichloromethane and an aliquot directly analyzed chromatographically using an HILIC column. Detection by mass spectrometry: monitoring the transition between the pseudo molecular ion ([M+H]+ a m/z 163) and the fragment at m/z 117. The procedure uses a deuterated internal pattern D4-nicotine, which monitors the equal transition (m/z 167-- > 121). The established limit of quantification is 0.5 ng (nanogram) of nicotine in the sample (e.g. 0.05 ng/mg in 10 mg simple).

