### Follow-up period

The follow-up period is six months from the start of the intervention.

A visit will be conducted by the pediatrician/nurse at three and six months after the start of the study. They will register the parents' tobacco habit and the level of ETS exposure obtained by a questionnaire (at three and six months) and the nicotine in hair (at six months).

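### Spring and fall visits do not give hair nicotine a similar climate, and the article states no maximum hair length to keep pre-intervention growth out of the six-month sample

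*Protocol article*

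**What the plan says.** Four parts of the protocol article bear on this.

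- **Timing.** Study period places recruitment in spring and "the six-month control visit in the fall, in order to compare the degree of exposure in a similar climate period".
- **Sampling.** Data collection procedures states that "a sample of the baby's hair will be taken at the first (recruitment) visit and at the last (six-month) visit". On how it is taken: "A lock of hair will be cut from the root and once collected, will be placed on a card". It refers to Additional files 1 and 2 for the study materials; these are not shown.
- **What hair measures.** Description of laboratory analysis technique presents hair as a marker of average or long-term exposure. It gives the growth rate ("As hair grows in average at a rate of one centimetre per month") and the consequence: "nicotine concentrations found in a segment of hair are related to the exposure during a period of time depending on the distance from the root". The assay steps then start from an amount, not a length: "The hair samples (several milligrams) are extensively washed with dichloromethane".
- **Use of the result.** Follow-up period states: "The follow-up period is six months from the start of the intervention". Sample size powers a 30% between-group difference in hair nicotine at the end of the intervention. Statistical analysis names hair nicotine as the principal variable. Results frames the primary result as a reduction in exposure between recruitment and six months, with hair nicotine as its objective measure.

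**The concern.** The timing rationale matches the weather around the visit dates. Hair looks backwards from the visit, so what needs matching is the period in which the assayed hair grew. Since the article itself treats climate as relevant to a baby's exposure, an unmatched growth period can move hair nicotine between the two samples without any intervention. A reduction seen within one arm could then be partly seasonal.

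The second issue is length. By the stated growth rate, hair more than 6 cm from the root at the final visit grew before the intervention began. The article sets no upper limit on the length assayed. If long locks are assayed whole, the six-month value mixes exposure from before and after the start of the intervention, and the between-arm difference shrinks towards zero.

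**Working it through.** **Inputs.** Growth 1 cm per month (Description of laboratory analysis technique). Samples six months apart (Data collection procedures). Data collection March to December 2009 (Study period). Mean 6.83 and SD 8.88 ng/mg, 30% difference, alpha 0.05, power 80%, 295 per group (Sample size). Two-sided tests (Statistical analysis). Hair lengths are **assumed**; the article gives none.

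**1. The plan's own figure.** The difference is 0.30 × 6.83 = 2.049 ng/mg. Then n = 2 × (1.960 + 0.842)² × 8.88² / 2.049² = 2 × 7.849 × 78.85 / 4.198 = 294.8, so 295 per group. The stated figure reproduces, and it belongs to a between-group comparison at the final visit.

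**2. Growth periods.** A root-cut lock of L cm taken at month t covers t − L to t. Its six-month pair covers t + 6 − L to t + 6. The two periods are six months out of phase for every L.

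| Visits | Length | Recruitment sample covers | Six-month sample covers |
|---|---|---|---|
| mid-March, mid-September | 3 cm | mid-December to mid-March | mid-June to mid-September |
| mid-March, mid-September | 6 cm | mid-September to mid-March | mid-March to mid-September |
| mid-April, mid-October | 3 cm | mid-January to mid-April | mid-July to mid-October |

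**3. How uneven the climates are.** Assume, for illustration, that climate follows a cosine of amplitude 1 with its warmest point about 1 August (month 7.0, counting from 1 January). The spring-minus-fall gap in the average over the growth period is

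gap = 2 × [sin(πL/12) / (πL/12)] × cos(2π(t − L/2 − 7)/12).

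Example: mid-March (t = 2.5) and 3 cm give 2 × 0.900 × (−1) = −1.80. The largest possible gap is 2; the visit-day column is the limit as L goes to 0.

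| Recruitment | Visit day | 1 cm | 3 cm | 6 cm |
|---|---|---|---|---|
| mid-March | −1.41 | −1.71 | −1.80 | −0.90 |
| mid-April | −0.52 | −0.99 | −1.56 | −1.23 |
| mid-May | +0.52 | 0.00 | −0.90 | −1.23 |
| mid-June | +1.41 | +0.99 | 0.00 | −0.90 |

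In mid-April the visit days are fairly close (0.52), but 3 cm of hair is not (1.56). The gap disappears for some combinations: 1 cm in mid-May, 3 cm in mid-June, 9 cm in mid-March, and any 12 cm sample. These are climate units. The article gives nothing that would convert them to ng/mg.

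**4. Pre-intervention hair in the six-month lock.** For L above 6 cm the share grown after the start is 6/L. Assume nicotine is deposited evenly along the hair, the arms are equal before the start, and a 30% difference applies to all hair grown afterwards. The apparent difference is then 30% × 6/L.

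| Assumed length | Share grown after start | Apparent difference |
|---|---|---|
| 6 cm or less | 100% | 30% |
| 8 cm | 75% | 22.5% |
| 9 cm | 67% | 20% |
| 12 cm | 50% | 15% |

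**The case against.** **The article may simply be silent on length.** Segment length is a sampling or laboratory detail that a condensed article can leave to fuller documents, and Additional files 1 and 2 may fix it. Cutting at the root is also what segment analysis requires. This stands: the length point applies only if no limit is set elsewhere. A reader might infer that whole locks are certain to be assayed, but the article does not say so.

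**No hair lengths are given.** Many babies in this age range may have 6 cm or less at the final visit, and then there is no dilution. A reader might turn the table into a loss of power: with 295 per group and the SD held at 8.88, 8 cm gives 56% and 12 cm gives 29%. Those figures follow arithmetically, but they rest on assumed lengths and an SD that need not stay fixed as the growth period lengthens. They also treat the planned 30% as a difference in underlying exposure, whereas Sample size states it for the measured nicotine. The article does not support any of them as this trial's power.

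**Season is common to both arms.** This stands. A reader might infer that the seasonal mismatch biases the trial's main comparison. It does not, provided both arms recruit over the same calendar, and the article gives one recruitment period for all teams. Statistical analysis plans control-versus-intervention comparisons. What remains is the framing of the primary result as a reduction from recruitment.

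**The climate sentence is about exposure in general.** Exposure is also recorded by questionnaire, for which visit timing may be a fair rationale. But the sentence carries no restriction, and hair nicotine is the principal variable.

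**The two problems do not peak together.** Short hair carries the seasonal gap without dilution; at 12 cm dilution is large but the seasonal gap is nil. They should not be added up.

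**Conclusion.** The concern holds in two limited parts.

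1. **Season, the firmer part.** The similar-climate rationale in Study period conflicts with the retrospective reading of hair in Description of laboratory analysis technique. For March and April recruitment with up to about 6 cm of hair, the samples compare mainly winter with mainly summer exposure. The conflict is weak or absent for late-spring recruitment with short hair. It affects the interpretation of within-arm change and leaves the randomised comparison at six months intact. Its size in nicotine units cannot be derived from the article.

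2. **Length, conditional.** As the article reads, nothing keeps pre-intervention hair out of a six-month lock longer than 6 cm. If such locks are assayed whole, the between-arm difference is multiplied by 6/L. A 30% difference becomes 22.5% at an assumed 8 cm and 15% at an assumed 12 cm; at 6 cm or less nothing is lost. How many babies are affected is unknown.

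**What to change.** - **Sampling and laboratory instructions.** Unless they already do so, state that at most the 6 cm nearest the root is assayed at the six-month visit. The cost is one line of instruction and slightly less hair mass in babies with long hair, hence possibly a few more values near the 0.5 ng quantification limit. Babies with shorter hair are unaffected. An identical segment length at recruitment is not needed and often not attainable: at 1 cm per month a two-month-old has about 2 cm.
- **Study period.** Restrict the similar-climate rationale to the questionnaire, or delete it for hair nicotine. Capping the length does not repair the seasonal mismatch, so this change is needed separately. It costs nothing.
- **Results and Statistical analysis.** State that effectiveness is judged on the between-arm difference in hair nicotine at six months, adjusted for the recruitment value, and that within-arm reduction is descriptive. This agrees with the comparison on which the trial is powered and requires no further data.

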### Description of laboratory analysis technique

Measuring nicotine in hair provides better information about average or long-term exposure to ETS as compared to other biological markers such as cotinine in the urine, saliva or blood, which have a shorter retrospectivity [28-32,37]. As hair grows in average at a rate of one centimetre per month, nicotine concentrations found in a segment of hair are related to the exposure during a period of time depending on the distance from the root. It is a specific biological indicator, sensitive, stable over time and temperature, not influenced by specific exposures prior to the analysis and easy to obtain [38,39]. The same IMIM team, with broad experience with the technique, analyzed all the samples. The analytical procedure of nicotine in hair utilizes ultra performance liquid chromatography (UPLC) coupled to tandem mass spectrometry (MS/MS) using a triple quadrupole instrument. The hair samples (several milligrams) are extensively washed with dichloromethane to eliminate any superficial contamination. Then hair samples are dissolved in an alkaline (1 M potassium hydroxide) solution. The nicotine released from the matrix of hair is extracted using dichloromethane and an aliquot directly analyzed chromatographically using an HILIC column. Detection by mass spectrometry: monitoring the transition between the pseudo molecular ion ([M+H]+ a m/z 163) and the fragment at m/z 117. The procedure uses a deuterated internal pattern D4-nicotine, which monitors the equal transition (m/z 167-- > 121). The established limit of quantification is 0.5 ng (nanogram) of nicotine in the sample (e.g. 0.05 ng/mg in 10 mg simple).

### Description of the intervention

Once the teams have shown interest in collaborating in the study, the participating teams will be randomly assigned by clusters to the intervention or control group, as specified in the methodology.

There will be three visits (at the start of the study, at three and six months after inclusion in the study for each baby included in the study (control and intervention group). These visits will be used to collect necessary information.

The teams included in the intervention group will be given a two-hour specific training on passive smoking, epidemiology, morbimortality and how to intervene in the reduction of ETS. The proposed intervention is based on interventions recommended in primary care that follow international and national clinical practice guidelines [13,35,36]. The intervention is based on counseling, cognitive theory and motivational interviewing.

Thus, this study is proposing a passive smoking intervention that has been adapted from an intervention that has been shown to be effective in decreasing active tobacco consumption in Primary Care.

The intervention aims to give parents that smoke brief information that emphasizes the health benefits that reducing ETS can have on their children. The basic elements of the intervention include:

1. Ask: whether or not there is a smoker that lives with the baby. If the answer is affirmative, the baby's level of exposure will be asked.

2. Assess knowledge: Information that the parents have about the effect of passive smoking in infancy.

3. Personalized information depending on the exposure and the perceived risk.

4. Ask about suggestions to make changes: support any efforts to modify exposure to ETS and discuss the problems this entails.

5. Personalized help and advice according to exposure, baby's background, perceived risk and parents' attitude towards making changes. This intervention will be reinforced with educational leaflets about passive smoking in infancy designed for the study (Additional file 3).

6. Congratulate if the mother and/or father has quit smoking during the pregnancy and support-encourage continued smoking cessation.

7. Support and encourage those that decide to quit smoking or reduce tobacco consumption.

The control group teams will conduct the three proposed visits during the six-month follow-up period. Aside from collecting the study variables, the control group will carry out the protocol's habitual care for a healthy child during the corresponding visits. In Catalonia, these visits are officially scheduled and include a generic reference to avoid exposure to air polluted by cigarette smoke; however, there is no specific protocol for action.

### Database

The database will be obtained from medical records, questionnaires (interviews or visits), biological hair samples from the babies in the first visit and from expired carbon monoxide (CO) of parents that claim to have quit smoking.

### Follow-up period

The follow-up period is six months from the start of the intervention.

A visit will be conducted by the pediatrician/nurse at three and six months after the start of the study. They will register the parents' tobacco habit and the level of ETS exposure obtained by a questionnaire (at three and six months) and the nicotine in hair (at six months).

### Statistical analysis

Statisticians from the University of Girona's Research Group in Statistics, Applied Economics and Health (GRECS) will carry out the statistical analyses. These statisticians will have an advisory role.

The data will be incorporated into a database constructed using SPSS version 15.0. The descriptive analyses, as well as the statistical hypothesis testing, will also be conducted with this program. For subsequent modeling, the Free R software (version 11.0 or later) will be used.

All of the known potential confounding factors will be measured at the beginning of the study, including the caretaker who smokes (and the stage of change), level of education, marital status, breastfeeding and other members of the household, overcrowding. Therefore, the control and intervention group comparisons will be carried out both adjusted and unadjusted for these known confounders.

The simple treatment effect without adjusting the rates, relative risks and the 95% confidence intervals will be obtained in the first case, with a subsequent adjusted multiple regression analysis for other variables. Two forms of regression analysis will be taken into account for the primaries.

Expected results: A Poisson regression analysis and a negative binomial if there is evidence of over or under dispersion. The analysis of the secondary results will be carried out using standard statistical procedures applicable to categorical or continuous data. An adjustment for protocol analysis will also be conducted to verify the robustness of the results. All tests of significance will be two-tailed. For the treatment effects, sensitivity analyses will be conducted to determine the effect of the missing data.

The analysis will be done following the following study phases:

1. Describe the effect in both groups:

Initially an analysis of baseline comparability will be carried out in relation with the study variables. The following step will be to estimate the effect on the response variables without adjusting for other variables. To perform the above analyses, chi-squared tests will be used for qualitative variables and comparison of means for quantitative variables.

2. To estimate the adjusted effect, a multivariate multilevel model will be used. The dependent or principal variable is the child's exposure using the measure of nicotine in hair. The baby's age and sex, as well as the variables that have been shown to be statistically significant, will be included in the bivariate analyses. The basic care unit and the individual will be the levels in the multilevel analysis.

3. Concordance between the filled questionnaire and the nicotine collected in the hair: a summary evaluation of the questionnaire on a discrete, quantitative scale based on the data that is provided by the number of smoking cohabitants, the number of cigarettes that they smoke and the exposure time outside of the home. Pearson's (or Spearman's depending on the distribution) correlation coefficient will be calculated between the estimate and the result obtained in the nicotine hair analysis. The intraclass correlation coefficient will also be studied between both measures. Finally, both estimates will be dichotomized (questionnaire and nicotine in hair analysis) into two categories (exposed/not exposed) and the Kappa coefficient between the two will be calculated.

In all cases a bilateral alpha error of 0.05 and a 95% confidence interval will be used. To complete the explicit information, the comparison of means will be performed using a Student's t-test for parametric variables and the U Mann-Whitney test for non-parametric variables.

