## Methods/Design

### Study design

Multi-centric, open cluster randomized field trial. Unit of randomization: Primary Care teams formed by a pediatrician and a pediatric nurse, both responsible for the same infant population.

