### Sample size

Based on the data from the pilot study in 46 babies and using the same analysis technique of nicotine in hair used in the present study, a mean of 6.83 ng/mg and a standard deviation of 8.88 ng/mg have been obtained. Assuming a mean difference of 30% between the intervention group and the control group in nicotine in hair at the end of the intervention, with an alpha value of 0.05 and a power of 80%, 295 subjects are needed in each group. If we assume a loss of 20%, the sample size increases to 708 (354 in each group). It is considered feasible for each basic care unit to recruit eight babies in a period of two months. The estimates of the intra-cluster correlation coefficient in cluster randomized trials that evaluate the implementation of clinical practice guidelines using outcome variables in primary healthcare are generally less than 0.05 [34]. These intra-cluster correlation coefficients translate to a cluster size of eight in a design effect corresponding to a factor of 1.4. Therefore, the final simple size will be 992 babies (446 in each group).

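### Unadjusted between-arm effects are tested at the level of the baby although teams are randomised: a nominal 5% test has a true size of about 6% to 9%, and only the adjusted hair-nicotine model has a team level

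*Protocol article*

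**What the plan says.** Study design fixes the unit of allocation: "Unit of randomization: Primary Care teams formed by a pediatrician and a pediatric nurse". Sample size accounts for this. It takes an intra-cluster correlation that is usually below 0.05 and eight babies per team, and applies a design effect of 1.4.

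The Statistical analysis section promises arm comparisons both with and without adjustment for confounders, including a simple treatment effect with relative risks and 95% confidence intervals. Its phases then read as follows.

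- **Phase 1** covers baseline comparability and then the unadjusted effect on the response variables. For these, "chi-squared tests will be used for qualitative variables and comparison of means for quantitative variables". The closing paragraph of the section says which comparison of means is intended: Student's "t-test for parametric variables and the U Mann-Whitney test for non-parametric variables". It also sets the error rate: "In all cases a bilateral alpha error of 0.05 and a 95% confidence interval will be used".
- **Phase 2** is a multilevel model for the adjusted effect, with the basic care unit and the individual as levels and hair nicotine as the dependent variable.
- **Phase 3** concerns agreement between questionnaire and hair nicotine, not a comparison of arms.

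For the remaining outcomes: "The analysis of the secondary results will be carried out using standard statistical procedures applicable to categorical or continuous data". For the primary results the section also names Poisson or negative binomial regression, with no team level stated. The Results section lists questionnaire-measured exposure among the primary results, together with hair nicotine.

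**The concern.** Babies cared for by the same paediatrician and nurse tend to resemble each other, and all of them receive the same arm. The chi-squared, Student's t and Mann-Whitney tests count each baby as an independent unit. When the intra-cluster correlation is positive, they understate the variance of the between-arm difference, so p-values are too small and confidence intervals too narrow.

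The protocol recognises this when it sets the sample size and when it models adjusted hair nicotine. It does not carry it into the unadjusted comparisons, for which it names tests that assume independence. It states nothing about clustering for the questionnaire-based primary result or for parental smoking. A trial report would therefore show unadjusted effects, with p-values and intervals, that cannot be taken at their nominal level next to an adjusted hair-nicotine effect that is not open to this objection.

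**Working it through.** **Inputs from the protocol**

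- Sample size: "a mean of 6.83 ng/mg and a standard deviation of 8.88 ng/mg have been obtained"; a 30% difference; "with an alpha value of 0.05 and a power of 80%, 295 subjects are needed in each group"; 20% losses, giving 708; correlation usually below 0.05; eight babies per team; design effect 1.4; final total 992.
- Statistical analysis: "All tests of significance will be two-tailed".

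**Step 1. Reproduce the plan's figures.** Difference = 0.30 × 6.83 = 2.049 ng/mg.

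n per group = 2 × (1.960 + 0.842)² × 8.88² / 2.049² ≈ 295, as printed.

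295 × 1.2 = 354 per group, or 708 in total. Design effect DE = 1 + (m − 1) × ICC = 1 + 7 × 0.05 = 1.35, which the plan rounds to 1.4. 708 × 1.4 = 991.2, hence 992. The plan's clustering inputs are therefore m = 8 and ICC = 0.05.

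**Step 2. True size of a test that ignores team.** The true variance of the difference is DE times the variance the test assumes. The test statistic under no effect is then spread by √DE, and

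true size = 2 × [1 − Φ(1.96 / √DE)].

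| Babies per team | ICC | DE | True size |
|---|---|---|---|
| 8 | 0.01 | 1.07 | 5.8% |
| 8 | 0.02 | 1.14 | 6.6% |
| 8 | 0.03 | 1.21 | 7.5% |
| 8 | 0.05 | 1.35 | 9.2% |
| 6.4 (8 × 0.8, after losses) | 0.05 | 1.27 | 8.2% |
| – | plan's rounded factor | 1.40 | 9.8% |

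At ICC 0.05 with eight per team, coverage of a nominal 95% interval is 100% − 9.2% = 90.8%.

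**Step 3. Check by simulation.** 8,000 trials with no effect, 62 teams of eight per arm (992 / 2 = 496 = 62 × 8). The protocol prints 446 per group, which is not half of 992, but the formula in step 2 depends only on DE. The continuous outcome is normal. The binary outcome has an assumed event rate of 10%, which is not in the protocol.

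| Test | ICC 0.01 | ICC 0.05 |
|---|---|---|
| Student's t on babies | 5.7% | 8.8% |
| Mann-Whitney on babies | 5.9% | 8.6% |
| Chi-squared on babies | 5.9% | 9.3% |
| t-test on team means (continuous) | 5.1% | 4.8% |
| t-test on team counts (binary) | 4.9% | 5.1% |

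All three named tests exceed 5% by about the amount the formula predicts. A simple team-level test on the same data returns to the nominal level.

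**Step 4. Cost in precision.** A valid interval is √DE times as wide: √1.35 = 1.16 at ICC 0.05, √1.07 = 1.03 at ICC 0.01.

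**The case against.** **The outcome that drove the sample size is analysed with clustering.** This stands. The adjusted hair-nicotine model has the basic care unit as a level. A reader might infer that the trial pays for clustering in its size and then ignores it in the analysis; the protocol does not support that as a general statement.

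**No test is named for the secondary outcomes.** This also stands. A reader might infer that parental cessation and reduction will be tested with chi-squared, t or Mann-Whitney tests. That is plausible, because phase 1 speaks of the response variables and the closing paragraph is general, but the text on secondary results commits only to standard procedures. An article may leave such detail to an analysis plan that is not shown. What can be said is that no cluster adjustment is stated for them.

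**About 9% is a ceiling.** Correct. The protocol describes correlations as generally below 0.05, so 9% should not be read as the expected error rate. It also gives no correlation specific to parental smoking.

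**Phase 1 is descriptive.** Its heading speaks of describing the effect, and part of it is baseline comparison, where a false-positive rate for treatment is not at issue. But the section also promises unadjusted treatment effects with relative risks, 95% intervals and two-sided tests. Those are inferential, and the tests are named, so for the unadjusted effect this is not a detail left open for a later document.

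**Mann-Whitney answers the skewness of nicotine.** The pilot SD (8.88) exceeds the mean (6.83), so skewness is a fair worry. A rank test on babies still ignores team, as the simulation shows.

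**Conclusion.** The point holds for the unadjusted between-arm effects: the protocol randomises teams and names tests that assume independent babies. For the questionnaire-based primary result and the secondary outcomes it holds in a weaker form: no cluster adjustment is stated. It does not touch the adjusted hair-nicotine model or the agreement analysis of phase 3.

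The size is moderate. With eight babies per team, a nominal 5% test has a true size between about 6% (ICC 0.01) and about 9% (ICC 0.05), and at the upper end 95% intervals cover about 91%. This rests on equal team sizes and on correlations at or below the plan's ceiling. For the secondary outcomes it also assumes that the same range applies and that the analysis would in fact ignore team.

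**What to change.** Reword the Statistical analysis section so that every between-arm inference respects team:

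- **Unadjusted effects:** use the phase 2 multilevel model with arm as the only covariate, or a test on team-level summaries. The latter is simple and also suits skewed nicotine.
- **Questionnaire exposure and parental smoking:** use mixed models, GEE clustered on team, or team-level summaries. If the Poisson or negative binomial regression is kept, state how team enters it.
- **Chi-squared, Student's t and Mann-Whitney on babies:** do not use them for between-arm inference.

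This needs a few lines of text and no additional data or recruitment. The cost is intervals up to about 16% wider at ICC 0.05 and about 3% wider at ICC 0.01. The wider intervals are the valid ones.
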